## 1. Introduction

**Background:** Diabetic retinopathy and Diabetic Macular Edema (DR) are the most common cause of blindness in the working population of the United States [1]. Each year, DR leads to more than 24,000 cases of preventable blindness in the United States. An estimated 4.1 million Americans are affected by DR including 899,000 with vision-threatening retinopathy [2].

Early detection of DR can prevent vision loss and blindness [3-7]; however, a large portion of individuals with diabetes do not currently undergo routine DR examinations [8]. In addition, specific disadvantaged groups have increased prevalence of diabetic retinopathy, where low rates of DR evaluation are at least partially associated with lack of access to a specialist exam [9].

FDA De Novo cleared IDx-DR, an autonomous artificial intelligence (AI) diagnostic system designed to detect DR in primary care [10]. Since its initial marketing in 2018, IDx-DR has been shown to address the unmet DR evaluation need, address the lack of access to care, and racial and ethnic disparities that have persisted for decades. IDx-DR was designed, developed, validated, and marketed under a strict ethical framework, which is documented in a series of publications through the Collaborative Community for Ophthalmic Imaging in which FDA participates [11]. IDx-DR is currently only indicated for use with one camera, Topcon NW400, for automatically detecting more than mild diabetic retinopathy (mtmDR), defined as ETDRS severity level 35 or higher, and or macular edema, in adult subjects diagnosed with diabetes not previously diagnosed with diabetic retinopathy.

FDA has requested a labeling extension to another camera as well as an eye-level analysis. This protocol and SAP addresses both needs.

**Scope:** The purpose of this study is to demonstrate that IDx-DR using the RetinaVue 700 Handheld Retinal Camera (RV700) is substantially equivalent to the predicate device, IDx-DR paired with the Topcon NW400, in terms of sensitivity and specificity, when compared at a per-eye level (a minimum of 200 eyes with mtmDR and 140 eyes without mtmDR). Success will be defined by demonstrating non-inferiority to the predicate device's performance levels at the eye-level. Additional analyses will be performed at the subject-level for regulatory submission and publication; this is consistent with the de novo study utilizing the Topcon NW400 retinal camera.

This study also includes a Precision Substudy to demonstrate the repeatability and reproducibility of IDx-DR with the RV700 using the same Latin Squares design as was used for the pivotal study. A total of 36 subjects who participated in the Diagnostic Performance Study will be invited to participate in the Precision Substudy. Of these 36 subjects, 18 will have received a PRS determination of mtmDR(+) for at least one eye, and 18 will have received a PRS determination of mtmDR(-) for both eyes. Each participating subject will undergo a series of nine imaging sessions with three different cameras, three operators, and three replicates to test the reproducibility and repeatability of using IDx-DR with the RV700. Analyses will be conducted at the eye-level as well as at the subject-level.

[figure not shown]

|                     |               |        |             |
|---------------------|---------------|--------|-------------|
| CTMF-SA-DXSDR006-03 | SAP_2.1_clean | Rev. A | Pg. 3 of 16 |
|---------------------|---------------|--------|-------------|

## 2. Study objectives and endpoints

| Objectives                                                                                                                                                                                                                                                                                                                                                                                                                                                                                       | Endpoints                                                                                                                                                                                                                                                                                                                                                                                                                                                                                                                                                                                                                                                                                                                                                                                                                                                                                                                                                                                                                                                                                                                                    |
|--------------------------------------------------------------------------------------------------------------------------------------------------------------------------------------------------------------------------------------------------------------------------------------------------------------------------------------------------------------------------------------------------------------------------------------------------------------------------------------------------|----------------------------------------------------------------------------------------------------------------------------------------------------------------------------------------------------------------------------------------------------------------------------------------------------------------------------------------------------------------------------------------------------------------------------------------------------------------------------------------------------------------------------------------------------------------------------------------------------------------------------------------------------------------------------------------------------------------------------------------------------------------------------------------------------------------------------------------------------------------------------------------------------------------------------------------------------------------------------------------------------------------------------------------------------------------------------------------------------------------------------------------------|
| Primary                                                                                                                                                                                                                                                                                                                                                                                                                                                                                   |                                                                                                                                                                                                                                                                                                                                                                                                                                                                                                                                                                                                                                                                                                                                                                                                                                                                                                                                                                                                                                                                                                                                              |
| 1. To demonstrate the substantial equivalence of IDx-DR using the RV700 to the predicate device (IDx-DR using the NW400) in detecting ETDRS level 35 or higher and/or DME                                                                                                                                                                                                                                                                                                                        | 1. Sensitivity and specificity of IDx-DR using RV700 based on eye-level results against a Level I Prognostic Reference Standard (PRS)
2. Eye-level sensitivity calculated using weighted sampling so that ETDRS level 53 or higher represents 20% of the mtmDR(+) sample                                                                                                                                                                                                                                                                                                                                                                                                                                                                                                                                                                                                                                                                                                                                                                                                                                                                  |
| Secondary                                                                                                                                                                                                                                                                                                                                                                                                                                                                                 |                                                                                                                                                                                                                                                                                                                                                                                                                                                                                                                                                                                                                                                                                                                                                                                                                                                                                                                                                                                                                                                                                                                                              |
| 1. To determine IDx-DR (using RV700) diagnosability, the percentage of eyes for which a diagnostic result can be provided.
2. To determine IDx-DR (using RV700) diagnosability, the percentage of subjects for which a diagnostic result can be provided.
3. To determine the positive and negative predictive values.
4. To investigate the effect of cases where no diagnostic result can be provided on sensitivity and specificity using a “worst case scenario” analysis approach. | 1. Sensitivity and specificity of IDx-DR using RV700 based on subject-level results against a Level I Prognostic Reference Standard (PRS)
2. Sensitivity and specificity of IDx-DR using RV700 based on eye-level results when compared to the Wisconsin Fundus Photograph Reading Center Level II Standard grading of the RV700 images
3. Sensitivity and specificity of IDx-DR using RV700 based on subject-level results when compared to the Wisconsin Fundus Photograph Reading Center Level II Standard grading of the RV700 images
4. Percent of total cases where a diagnostic result can be provided by IDx-DR with the RV700
5. Positive Predictive Value (PPV) and Negative Predictive Value (NPV) of IDx-DR with the RV700; repeat PPV and NPV calculations using the above weighted samples
6. Sensitivity and specificity of IDx-DR categorizing all PRS-determined positive cases with no diagnostic result as false negatives and all PRS-determined negative cases with no diagnostic result as false positives, i.e., a “worst case scenario” analysis of the impact of “Exam Quality Insufficient” results |
| Precision Substudy                                                                                                                                                                                                                                                                                                                                                                                                                                                                        |                                                                                                                                                                                                                                                                                                                                                                                                                                                                                                                                                                                                                                                                                                                                                                                                                                                                                                                                                                                                                                                                                                                                              |

[figure not shown]

| CTMF-SA-DXSDR006-03                                                                                                                                                                                                                              | SAP_2.1_clean                                                                                                                                                                                                                                                                                                                                                                                                                                                                                                                                                                                                                                                       | Rev. A | Pg. 4 of 16 |
|--------------------------------------------------------------------------------------------------------------------------------------------------------------------------------------------------------------------------------------------------|---------------------------------------------------------------------------------------------------------------------------------------------------------------------------------------------------------------------------------------------------------------------------------------------------------------------------------------------------------------------------------------------------------------------------------------------------------------------------------------------------------------------------------------------------------------------------------------------------------------------------------------------------------------------|--------|-------------|

**Supplementary Table 1: Eye-level diagnostic design parameters and pivotal study subject-level performance**

|             | Eye-level
Null Hypothesis
$p_0$ | Subject-level
Point Estimate
(two-sided 95% CI) |
|-------------|---------------------------------------|-------------------------------------------------------|
| Sensitivity | 75.0%                                 | 87.2% (81.8-91.2%)                                    |
| Specificity | 77.5%                                 | 90.7% (88.3-92.7%)                                    |

The primary efficacy analysis for the eye-level sensitivity analysis will be repeated for Level 1 using overweight sampling to achieve 20% mtmDR(+) with ETDRS level 53 or higher.

In addition, the primary analyses will be performed at the subject-level for regulatory submission and publication; this is consistent with the de novo study utilizing the Topcon NW400 retinal camera.

[figure not shown]

|                     |               |        |             |
|---------------------|---------------|--------|-------------|
| CTMF-SA-DXSDR006-03 | SAP_2.1_clean | Rev. A | Pg. 5 of 16 |
|---------------------|---------------|--------|-------------|

**2.2 Diagnostic Performance Study Secondary endpoints:** Secondary endpoints include estimation of test characteristics including positive predictive value (PPV), negative predictive value (NPV), and diagnosability. Other secondary endpoints include calculations of sensitivity and specificity that include each test's respective ungradable eyes in the denominator (see [Supplementary Table 2](#) below). One-sided 97.5% confidence intervals that account for inter-eye correlation will be presented as a measure of precision for all point estimates.

For secondary efficacy endpoints, the following will be analyzed:

- 1) Diagnosability: the percentage of total cases where a diagnostic result can be provided by IDx-DR with the RV700
- 2) Positive Predictive Value (PPV) and Negative Predictive Value (NPV) of IDx-DR with the RV700;
- 3) Sensitivity and specificity of IDx-DR as if all PRS-determined positive cases with no diagnostic result provided were false negatives and all PRS-determined negative cases with no diagnostic results were false positives, i.e., a "worst case scenario" analysis of the impact of "Exam Quality Insufficient" results
- 4) Sensitivity and specificity of IDx-DR using RV700 based on eye-level results when compared to the Wisconsin Fundus Photograph Reading Center (FPRC) Level II Standard grading of the RV700 images.

The corresponding PPV and NPV from weighted sampling will also be computed; the same specificity population will be used for these additional calculations.

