#### 4. Sample size calculations

**Assumptions:** In this study, a minimum of 200 eyes with mtmDR and at least 140 eyes without mtmDR will be enrolled in the main diagnostic performance study; enrollment will be continued until a minimum of 20 vtDR eyes are confirmed to be sufficient and gradable. The device performance will be evaluated per eye. The primary endpoints will be the sensitivity and specificity of IDx-DR paired with the RV700 in detecting mtmDR based on eye-level results when compared to a PRS by three retinal experts.

[figure not shown]

|                     |               |        |             |
|---------------------|---------------|--------|-------------|
| CTMF-SA-DXSDR006-03 | SAP_2.1_clean | Rev. A | Pg. 8 of 16 |
|---------------------|---------------|--------|-------------|

The predicate device, IDx-DR with the NW400, pivotal trial pre-specified null hypotheses for sensitivity and specificity of 75% and 77.5%, respectively; these represent pre-defined non-inferiority margins. The alternative hypotheses were 85.0% for sensitivity and 82.5% for specificity in support of a non-inferiority design. These lower thresholds for performance will be ruled out with one-sided 97.5% confidence bounds.

As this study is intended to support an extension of the IDx-DR labeling to validate a new camera for use with IDx-DR, the performance is expected to be substantially equivalent to the predicate device at the subject-level.

This study will validate the use of a new camera with the same diagnostic algorithm as currently on the market. The proposed sample size maintains a one-sided 97.5% confidence interval that exceeds the predicate device pivotal trial null hypotheses, i.e., a lower confidence limit  $> 75\%$  for sensitivity and  $> 77.5\%$  for specificity which reflects a 5% non-inferiority offset for sensitivity and a 2.5% non-inferiority offset for specificity (see **Supplementary Table 3** columns 1-4). These hypothesis tests were designed specifically to reflect clinically meaningful eye-level outcomes; substantial equivalence is interpreted as non-inferiority

(**Supplementary Table 3** columns 1-4).

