**Supplementary Table 3: Power and Significance Threshold Calculations Summary (minimum sample sizes)**

|                                   | Sponsor Criteria (Non-inferiority) |       |             |       |
|-----------------------------------|------------------------------------|-------|-------------|-------|
|                                   | Sensitivity                        |       | Specificity |       |
|                                   | Power                              | N-I   | Power       | N-I   |
|                                   | 1                                  | 2     | 3           | 4     |
| Test significance level, $\alpha$ | 0.025                              | 0.025 | 0.025       | 0.025 |
| 1 or 2 sided test?                | 1                                  | 1     | 1           | 1     |
| Null hypothesis %, $\pi_0$        | 75%                                | 75%   | 77.5%       | 77.5% |
| Alternative hypothesis %, $\pi_A$ | 83.5%                              | 81.2% | 87.1%       | 84.6% |
| Power (%)                         | 80                                 | NA    | 80          | NA    |
| N                                 | 200                                | 200   | 140         | 140   |

**Supplementary Table 4** summarizes the study design parameters inclusive of:

- the eye-level hypotheses to be tested (non-inferiority)
- the non-inferiority thresholds and offsets
- the sample size requirements, and
- the thresholds needed to establish non-inferiority.

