**Supplementary Table 4: Inputs to power calculations for one-sided exact binomial tests**

| Sensitivity                                                                     | Specificity                                                                        |
|----------------------------------------------------------------------------------------|-------------------------------------------------------------------------------------------|
| $H_0: P \leq 0.75$ vs. $H_1: P > 0.75$                                                 | $H_0: P \leq 0.775$ vs. $H_1: P > 0.775$                                                  |
| $p_{baseline} = 0.80$ is the sensitivity target                                        | $p_{baseline} = 0.80$ is the specificity target                                           |
| $p_0 = 0.75$ sensitivity values below 75% are considered inferior to IDx-DR with NW400 | $p_0 = 0.775$ specificity values below 77.5% are considered inferior to IDx-DR with NW400 |
| $p_1 = 0.835$ hypothesized sensitivity of IDx-DR with RV700                            | $p_1 = 0.871$ hypothesized specificity of IDx-DR with RV700                               |

[figure not shown]

| CTMF-SA-DXSDR006-03                                                                                                                                                                   | SAP_2.1_clean                                                                                                                                                                         | Rev. A | Pg. 9 of 16 |
|---------------------------------------------------------------------------------------------------------------------------------------------------------------------------------------|---------------------------------------------------------------------------------------------------------------------------------------------------------------------------------------|--------|-------------|
| $d_0 = -0.05$ non-inferiority difference.
$d_0 = p_0 - p_{baseline}$ and is the maximum distance that may still be considered non-inferior.                                        | $d_0 = -0.025$ non-inferiority difference.
$d_0 = p_0 - p_{baseline}$ and is the maximum distance that may still be considered non-inferior.                                       |        |             |

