## 5. Analysis

**5.1 Diagnostic Performance Study:** A cross tabulation of IDx-DR results (positive, negative, ungradable) with the results from the reference standard (positive, negative, ungradable) will be presented for the overall sample. The point estimate for each test characteristic will be presented along with the counts of eyes (numerator and denominator) that contribute to the calculation. One-sided 97.5% confidence intervals will be computed by the cluster bootstrap approach to account for correlation introduced by taking measurements from both eyes of each subject; in cases where the confidence interval is not estimable using the cluster bootstrap approach due to small sample sizes or boundary values (e.g., a test characteristic of 100%), the exact binomial confidence interval will be presented instead. Primary endpoints will be reported in stratified

[figure not shown]

|                     |               |        |              |
|---------------------|---------------|--------|--------------|
| CTMF-SA-DXSDR006-03 | SAP_2.1_clean | Rev. A | Pg. 10 of 16 |
|---------------------|---------------|--------|--------------|

analyses by eye, age, sex, and race/ethnicity. Should enrichment be implemented, further stratification of all endpoints will be presented by cohort: sequential enrollment or enrichment.

The sensitivity, PPV, and NPV analyses will be repeated in the same manner for the weighted samples. The PPV and NPV calculations will be performed using the accrued specificity data without any resampling of eyes with ETDRS level less than 53.

Relevant data analyses will be repeated at the subject-level for regulatory submission and publication consistent with the de novo study utilizing the Topcon NW400 retinal camera.

Data analysis will be performed using SAS (V9.3 or later).

**Population:** We anticipate those recruited will mirror the spectrum of disease severity encountered at primary care settings and be similar to the study population in the pivotal trial. [10] In the analyzable population, 30.9% were  $\geq 65$  years old, 16.4% were Hispanic, 28.2% Black, and 86.7% had HbA1c  $\geq 7$ .

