#### 7.4. Enrichment Cohort

In order to assure an adequate range of DR conditions in the study population sample, and avoid spectrum bias, for sensitivity and specificity analysis, the primary care study population may be enriched following the pre-specified formal evaluations outlined in the Data Transfer Plan, to ensure a sufficient range of diabetic retinopathy severity within cases. The enrichment cohort will be targeted using HbA1c levels, if needed, and will draw from the same pool of intent to screen subjects as the non-enriched subjects. To avoid excessive enrollment in any one stratum, the totals will be monitored weekly. Participant enrichment will be targeted based on elevated HbA1c, factors which have been shown to be correlated with higher rates of mtmDR among patients with diabetes. No cap will be placed on enriched participants since such participants will be prospectively recruited. The goal will be to recruit enough subjects to satisfy each stratum. If enrollment patterns are not on track with the study's target population after periodic reviews, enrollment at all sites will be adjusted monthly by modifying the HbA1c. Adjustments from this level may be instituted after a periodic review of the stratum enrollments reflecting the number of participants with diabetic retinopathy or diabetic macular edema. Study sites will be notified by the CRO if there is to be a change in the HbA1c thresholds. Once the total number of cases has been projected in alignment with statistical power requirements, then the final adjustments to participant enrollment criteria will be performed.

Monitoring of strata will be performed by the study statistician (without access to IDx-DR results); only available HbA1c, along with FPRC categorization into mtmDR and vtDR, will be visible for each subject included to date. The study statistician will notify the CRO whether updated HbA1c thresholds are needed. Again, once the strata targets for mtmDR and no/mild DR can be projected, the HbA1c thresholds will be locked.

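### Pooled PPV and NPV describe the recruited mix of eyes, which enrolment minima and possible HbA1c enrichment determine, and nothing in the plan standardises them to a primary-care prevalence

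*Combined protocol and SAP*

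**What the plan says.** SAP 2.2 names "Positive Predictive Value (PPV) and Negative Predictive Value (NPV) of IDx-DR with the RV700" as a secondary endpoint. The formulas in SAP 2.3 and protocol 9.3.3 are PPV = PP/(PP+PN) and NPV = NN/(NP+NN), with no prevalence term. SAP section 4 puts all recruited subjects into the final analyses.

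Four features bear on the mix of eyes:

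- **Minima and target.** SAP section 4 requires at least 200 mtmDR(+) and 140 mtmDR(-) eyes. It sets a target of 564 eyes from at most 282 subjects, and expects more than 450 negatives on the strength of a 1:4 historical enrolment ratio.
- **Enrichment.** Protocol 7.4 allows recruitment on raised HbA1c, with thresholds that can be changed monthly if enrolment is off track and that are later locked. It adds: "No cap will be placed on enriched participants since such participants will be prospectively recruited". Protocol 4.1 presents enrichment as certain; protocol 7.4 and 9.3.4 and SAP 5.1 present it as conditional.
- **Cohort split.** If enrichment is used, SAP 5.1 and protocol 9.3.4 report every endpoint separately for the sequential and enrichment cohorts.
- **Weighted repeat.** Eyes at ETDRS level 53 or higher are resampled with replacement. For this repeat SAP 5.1 states: "The PPV and NPV calculations will be performed using the accrued specificity data", so eyes below level 53 are left as accrued.

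SAP 3.1 and protocol 4.1 both expect the study population to resemble the disease spectrum of primary care.

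**The concern.** Sensitivity and specificity condition on disease status, so they can be estimated from a sample with an artificial share of diseased eyes. PPV and NPV cannot: a raw-count PPV is the PPV at the sample's own prevalence. Here that prevalence is steered by counts of reading-centre positives and negatives. If the recruited share is above the primary-care share, pooled PPV is too high and pooled NPV too low for the setting the study says it represents.

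The planned intervals would not reveal this. The cluster bootstrap in SAP 5.1 resamples participants within strata defined by number of eyes and number of mtmDR(+) eyes, so the recruited mix is held essentially fixed in every resample. A tight interval could therefore surround a value that does not apply to primary care.

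**Working it through.** **Planning values.** The plan gives no expected PPV or NPV, so the first step is to confirm the accuracy values that feed the calculation. SAP section 4 gives "pre-specified null hypotheses for sensitivity and specificity of 75% and 77.5%, respectively" and states "These lower thresholds for performance will be ruled out with one-sided 97.5% confidence bounds", so one-sided alpha is 0.025. Supplementary Table 4 gives 83.5% as the "hypothesized sensitivity of IDx-DR with RV700" and 87.1% as the "hypothesized specificity of IDx-DR with RV700". Exact one-sided binomial tests then give:

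- Sensitivity, n = 200: smallest rejecting count 163, alpha 0.0182, power 80.6%.
- Specificity, n = 140: smallest rejecting count 119, alpha 0.0181, power 80.9%.

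Both agree with the stated counts and with the 80% power in SAP Supplementary Table 3 ("Power and Significance Threshold Calculations Summary (minimum sample sizes").

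**mtmDR share of the recruited eyes.**

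- 1:4 ratio: 1/(1+4) = 20%.
- 200 positives with 450 negatives: 200/650 = 30.8%.
- 200 positives in 564 eyes: 200/564 = 35.5%.
- Both minima exactly: 200/340 = 58.8%.

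At 20%, 564 eyes would yield 564 × 0.20 ≈ 113 positives, and 200 positives would need 200/0.20 = 1,000 eyes. The 200-eye minimum therefore fits inside the target only if the share is at least 35.5%. The anticipated 200 + 450 = 650 eyes also exceeds 564.

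**PPV and NPV.** With prevalence π,

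PPV = Se·π / [Se·π + (1−Sp)(1−π)]

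NPV = Sp(1−π) / [Sp(1−π) + (1−Se)π]

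For 200 positive eyes the expected counts are 200 × 0.835 = 167 true positives and 33 false negatives. Each negative eye contributes 0.871 true negatives and 0.129 false positives.

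| Mix (positive:negative) | Share | PPV | NPV | Gap from 20% (PPV / NPV, points) |
|---|---|---|---|---|
| 200:800 | 20.0% | 167/270.2 = 61.8% | 696.8/729.8 = 95.5% | reference |
| 200:450 | 30.8% | 167/225.05 = 74.2% | 391.95/424.95 = 92.2% | +12.4 / −3.2 |
| 200:364 | 35.5% | 167/213.96 = 78.1% | 317.04/350.04 = 90.6% | +16.2 / −4.9 |
| 200:140 | 58.8% | 167/185.06 = 90.2% | 121.94/154.94 = 78.7% | +28.4 / −16.8 |

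**Dependence on the inputs.**

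- With the pivotal subject-level values (87.2%, 90.7%), the gaps at 200/650, 200/564 and 200/340 are 10.6, 13.6 and 23.0 points for PPV, and 2.5, 3.8 and 13.4 for NPV.
- With 80% for both, they are 14.0, 18.7 and 35.1 for PPV, and 4.1, 6.2 and 20.4 for NPV.
- With 564 eyes of which only 140 are negative, at the planning values, they are 33.3 and 31.9.
- With a reference prevalence of 25%, PPV is 68.3%, so the gaps at the two anticipated mixes fall to 74.2 − 68.3 = 5.9 and 78.1 − 68.3 = 9.8 points. At 10%, PPV is 41.8% and they rise to 32.4 and 36.3.

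**Weighted repeat.** Assume 20 of 200 positives are at level 53 or higher. Raising them to 20% needs x extra draws with (20+x)/(200+x) = 0.20, so x = 25. Positives rise to 225 with negatives unchanged. With 450 negatives, and the same sensitivity in the drawn eyes, PPV rises by about 2 points and NPV falls by about 1. The shift is small, and it moves away from a lower prevalence.

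**The case against.** The strongest reply has four parts.

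1. *The plan is not blind to prevalence.* SAP 5.1 says the weighted sampling is there to examine how prevalence affects PPV and NPV, and the cohort split would supply sequential-cohort values. Numerators and denominators accompany each estimate, so a reader could apply Bayes' rule unaided. This stands in part. However, the weighting can only raise prevalence, the cohort split depends on enrichment being used, and the pooled count remains the defined endpoint.

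2. *The 20% reference is not a primary-care prevalence.* This stands. It comes from an enrolment ratio, and the approximate 20% in protocol 4.1 is a share of subjects with one or both eyes affected. If eye-level prevalence at the sites really were near 35%, pooled values at that mix would be right for them. The direction of the error depends on true prevalence lying below the recruited share.

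3. *Enrichment may not happen.* This also stands. A reader might infer from protocol 4.1 that the sample will certainly be enriched, but protocol 7.4 and SAP 5.1 make it conditional. Consecutive enrolment without enrichment would leave the mix closer to that of the sites. Yet at the plan's own 1:4 ratio the target would yield only about 113 positives, so the minimum and the target together still require a higher share.

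4. *No decision depends on PPV or NPV.* This is correct. Success is defined on sensitivity and specificity, and no passage says the pooled predictive values will be presented as primary-care values.

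A reader might also take 28 and 17 points as the expected error or as a ceiling. The documents support neither: the figures need enrolment to stop exactly at 200:140, while SAP section 4 expects many more negatives, and other inputs drawn from the plan give larger gaps.

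**Conclusion.** The point holds as a reporting defect in a secondary endpoint. As defined, pooled PPV and NPV are values for the recruited mix, and the plan has no analysis that carries them to a stated primary-care prevalence. Relative to an assumed 20%, and at sensitivity 83.5% and specificity 87.1%, PPV would be about 12 to 16 points too high and NPV about 3 to 5 points too low at the mixes the plan anticipates. The 200:140 scenario gives about 28 and 17 points. These sizes rest on the planning accuracy, on the 20% reference and on the final mix, none of which is known in advance. The change is worth making before the data are analysed, so that the prevalence range is not chosen after results are seen.

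**What to change.** In SAP 2.2, 2.3 and 5.1 and protocol 9.3:

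- Define the reported PPV and NPV by Bayes' rule from the estimated eye-level sensitivity and specificity over a pre-specified prevalence range, for example 10% to 40%, with 20% labelled as an assumption.
- Take the intervals from the cluster bootstrap already planned, recomputing both quantities in each resample at each fixed prevalence.
- Keep the pooled raw-count and weighted values as descriptive results, labelled as specific to this sample, next to the sequential-cohort values if enrichment is used.
- State the mtmDR share of analysed eyes beside every raw value.

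The cost is SAP and protocol wording and a few lines of code, with no new data and no change to sample size. The downside for the sponsor is a less favourable reported PPV: at an assumed 20% and the planning values, 61.8% in place of 74.2% to 78.1%.
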